## Abstract

**Background:**

Potassium regulation in the body is primarily done in the kidney. In addition to this, hyperkalemia, occurs in approximately 10% of individuals with chronic kidney disease (CKD) and is associated with elevated all-cause mortality. Individuals with CKD are often told to restrict dietary potassium (K), however, this recommendation is based on low quality evidence. Reduced quality of life, limited dietary choices and nutritional deficiencies are all potential negative outcomes that may occur when restricting dietary K in CKD patients. There is a need for randomized controlled trials investigating the impact of dietary K modification on serum K concentrations in people with CKD.

**Methods:**

A randomized 2-period crossover design comparing a liberalized K fruit and vegetable diet where participants will be required to consume ~ 3500 mg of dietary K daily, to a standard K restricted diet where participants will be required to consume < 2000 mg of dietary K daily. All participants will begin on a liberalized K run-in period for 2 weeks where they will receive fruit and vegetables home deliveries and for safety will have clinical chemistry, including serum potassium measurements taken after 1 week. Participants will then be randomized into either liberalized K or standard K diet for six weeks and then crossover to the other intervention for another 6 weeks after a 2-week washout period.

**Discussion:**

30 male and female CKD outpatients, ≥ 18 years of age, who have an estimated glomerular filtration rate (eGFR) between 15 and 45 ml/min/1.73m^2^ and serum K between 4.5 and 5.5 mEq/L. This design would have greater than 80% power to detect a difference of 0.35 mEq/L serum K between groups. Anthropometric measurements, clinical chemistry, dietary recalls, physical function assessments, as well as a quality of life assessments will also be measured in this trial. These findings will provide high quality evidence for, or against, recommendations for dietary K restriction in individuals living with CKD. The removal of K restriction could provide individuals living with CKD more dietary choice leading to improved dietary status and quality of life.

**Trial Registration:**

This trial has received approval from the University of Manitoba Research Ethics board (HS25191 (B2021:104)).

**Supplementary Information:**

The online version contains supplementary material available at 10.1186/s12882-023-03354-4.

## Introduction

### Background and rationale

Chronic kidney disease (CKD) is a major public health concern with rising incidence and prevalence worldwide [1]. More than one in ten Canadians suffer from CKD, and it is currently a leading contributor to global morbidity, mortality, and increased healthcare costs [2, 3]. To help slow CKD progression, optimal management includes interventions such as blood pressure control, RAASi, and SGLT2i therapy [4, 5]. Equally as important are management of its complications, which include anemia, metabolic acidosis, mineral bone disorder and hyperkalemia [6].

The kidney is the primary site of potassium (K) regulation in the body. Hyperkalemia, elevated serum K (sK) occurs in approximately 10% of individuals living with CKD and is associated with elevated all-cause mortality. Hyperkalemia may result from many factors that influence both internal and external K regulation. Comorbid conditions commonly found in patients with CKD such as diabetes mellitus and metabolic acidosis, as well as the use of RAASi and K sparing diuretics, are associated with hyperkalemia [7]. Potassium binders exist, but they are poorly tolerated, can cause rare but fatal gastrointestinal side effects [8], have insufficient long-term data and there is poor access for most Canadians due to cost [9]. Therefore, to minimize the risk of hyperkalemia, individuals living with CKD are often recommended to restrict dietary K (dK). A systematic review and meta-analyses done in 2019 showed that the recommendation to restrict dietary K is based on very-low quality evidence, mostly epidemiological studies and a single randomized controlled trial (RCT) involving individuals living with end stage renal disease (ESRD) who received only manufactured liquid diets with low K concentrations [10]. While the review authors concluded that it is prudent to continue to restrict dK based on low-quality evidence, definitive trials are needed to determine if dK restrictions lowers sK [10].

Diets rich in fruit and vegetables are also typically rich in K as well as other minerals, vitamins and fiber, and are a source of dietary bicarbonate [11]. High K diets, where the K is from fruit and vegetables, are associated with health benefits, including reduced risk of cardiovascular disease [12]. Regrettably, due to the K content fruit and vegetable intake is often reduced when dK is restricted. The benefit of restricting high K fruit and vegetables in terms of sK lowering may not be guaranteed because high K fruit and vegetables often contain carbohydrate, which promotes insulin secretion and K uptake into cells, therefore the impact of different sources of dK influence sK concentrations is not always predictable. Additionally, dK restrictions can negatively impact quality of life, dietary choices and may put participants at risk of nutritional deficiencies such as decreased calcium, therefore it is essential that such a restriction should be based on good quality evidence [13]. There is a clear need for high quality RCTs investigating the impact of dK modification on sK concentrations in individuals living with CKD.

### Objectives

The objectives of this trial are to evaluate the impact and safety of dK liberalization with fruit and vegetables on sK concentrations and to monitor the effects it may have on their physical function and overall quality of life in patients with CKD.

For this trial, our primary hypothesis is that liberalization of dietary K intake, via the provision of higher K fruit and vegetables will be non-inferior to the standard recommended CKD diet in terms of change in sK concentrations. We also hypothesize that liberalization of dietary K will improve self-reported quality of life and lower blood pressure.

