### Trial design

This study is an open-label, randomized 2-period crossover definitive superiority trial. The study will be sixteen weeks in duration. Thirty male and female individuals living with CKD will be recruited, with a minimum 40% of each sex. Participants will be randomized to receive both restricted (standard care) and liberalized (experimental) K content fruit and vegetables for six weeks.

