### Sample size

It has been estimated that a sample size of thirty individuals with each sex will provide 80% power to detect a minimal clinically important difference of 0.35mmEq/L, the reduction shown with a starting dose of Patiromer (4.2 g twice daily) in a double-blind placebo-controlled trial of patients with CKD and hyperkalemia [14]. This assumes a within-subject standard deviation of 0.46, based on a 95% confidence interval of (0.38, 0.72) mEq/L seen in a similar 29-participant cross-over study unpublished, summary results of NCT00949585 found in appendix of Marklund et al [15].

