### Statistical methods

The primary analysis will be based on sK concentration, comparing the endpoints of the intervention periods. The effects of treatment on primary and secondary outcomes using a linear mixed-effects model for the repeated measures will be examined (essentially a paired comparison of the endpoints of the standard care dK diet versus the experimental dK diet). Sex will be included in this model as a fixed factor. Model assumptions for outcome data will be verified by visual inspection of residual plots and through sensitivity analyses regarding missing value strategies. Outcomes which appear to violate the modelling assumptions may be transformed prior to analysis or analysed using another, more appropriate model (e.g., generalized linear mixed models) in supportive analyses. Demographic data will be reported as the mean ± standard deviation. Analyses of the secondary outcomes will be reported as unadjusted and adjusted (expected marginal) means with 95% confidence intervals.

The primary analysis will be conducted using the All Participants (intent to treat) analysis set. The primary analysis will be repeated in the Completers analysis set. Demographics and all other baseline measurements will be analyzed in the All Participants set as well as in the Completers set.

The number and proportion of missing values will be documented in the clinical study report. Missing values will not be imputed unless otherwise noted. Analyses will exclude data from participants who have missing values for any variable required for the analysis. When data are observed to be unusual in a way that cannot be explained or ruled to be in error, analyses may be repeated after excluding the record involved. These additional analyses will be presented as sensitivity analyses. Additionally, all protocol deviations documented in the clinical trial database will be tabulated (if appropriate) and listed in the clinical study report. In general, analyses resulting in p-values less than 0.05 will be described as statistically significant, without adjustment for multiple inference. All results arising from secondary, exploratory and supportive analyses will be identified as such. Overall, the analysis done in this trial is the similar to the ReDACKD clinical trial [16].

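### The primary hypothesis is non-inferiority, but the design, sample size and significance rule are those of a superiority trial, so the stated analysis cannot establish it

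*Protocol article*

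**What the plan says.** Four parts of the protocol article bear on this.

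- **Objectives.** The primary hypothesis is that the liberalized diet "will be non-inferior to the standard recommended CKD diet in terms of change in sK concentrations".
- **Trial design**, the next section: "This study is an open-label, randomized 2-period crossover definitive superiority trial".
- **Sample size.** Thirty participants are to give "80% power to detect a minimal clinically important difference of 0.35mmEq/L". The figure is taken from the effect of a potassium binder's starting dose and is not called a margin. The variability input reads: "This assumes a within-subject standard deviation of 0.46, based on a 95% confidence interval of (0.38, 0.72) mEq/L". The Abstract repeats the aim: "This design would have greater than 80% power to detect a difference of 0.35 mEq/L serum K between groups".
- **Statistical methods.** A mixed model, in effect a paired comparison of the period endpoints, is run by intention to treat and repeated in completers. The only decision rule is that "analyses resulting in p-values less than 0.05 will be described as statistically significant, without adjustment for multiple inference". No confidence limit is compared with a margin.

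**The concern.** A non-inferiority hypothesis is supported when the data exclude a harm as large as a stated margin. A superiority test asks whether the data exclude zero. The two can disagree on the same data, and the article names one in the hypothesis and the other in the design, the sample size and the decision rule.

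On serum potassium, the outcome favourable to the new diet is no important rise. Under p < 0.05, two kinds of result could seem to support that. One is significantly lower potassium on the liberalized diet, which would be real support. The other is a non-significant difference, which shows only that zero was not excluded. Noise makes the second more likely, and so does dropping participants with missing values, because it shrinks the sample. If the framework is settled only after the data are seen, the result can choose the test.

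**Working it through.** **Inputs.** N = 30, difference 0.35 mEq/L, SD 0.46 (Sample size); p < 0.05 (Statistical methods). Sidedness is not stated, so two-sided is assumed.

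**1. The plan's own figure.** If 0.46 is the within-subject SD, the SD of a paired difference is 0.46 × √2 = 0.651.

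- Normal approximation: N = 2 × [0.46 × (1.960 + 0.842) / 0.35]² = 2 × 3.683² = 27.1, so 28.
- Noncentral t: N = 30, with power 81% at 30 (28 df).
- A one-sided 5% test would need only 23.

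The stated 30 therefore reproduces as a two-sided test of a difference against zero.

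**2. Two readings of 0.46.** The quoted interval has half-width (0.72 − 0.38) / 2 = 0.17. Suppose, as an assumption, that it is a confidence interval for a diet contrast in the 29-participant crossover study the article cites. Then the SD of the paired difference in that study is 0.17 × √29 / 1.96 = 0.47 (normal) or 0.17 × √29 / 2.048 = 0.45 (t, 28 df). So 0.46 may already be the SD of the difference, and both readings are carried below.

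**3. Precision at N = 30**, with t(28) = 2.048:

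- SD of difference 0.651: SE = 0.651 / √30 = 0.119, half-width 0.24.
- SD of difference 0.46: SE = 0.46 / √30 = 0.084, half-width 0.17.

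**4. Chance of a non-significant result** (noncentral t, 28 df, noncentrality = true rise / SE):

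| True rise on liberalized diet (mEq/L) | SD of difference 0.651 | SD of difference 0.46 |
|---|---|---|
| 0.35 | 19% | 2% |
| 0.25 | 47% | 18% |
| 0.20 | 63% | 37% |

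A confidence-limit test with margin 0.35 would wrongly conclude non-inferiority in 2.5% of trials at a true rise of 0.35, on either reading.

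**5. How the frameworks diverge.** With half-width 0.24, an estimate of 0.20 gives −0.04 to 0.44: not significant, yet 0.35 is not excluded. With half-width 0.17 the same estimate gives 0.03 to 0.37, which is significant, so this example depends on the SD reading. On that second reading the opposite conflict can arise. The interval's full width is 2 × 0.172 = 0.344, so it can just fit between 0 and 0.35: a significant rise that is also non-inferior at that margin.

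**6. Power at N = 30 for a non-inferiority test** (one-sided 0.025, noncentral t). The article gives no margin, so a range is shown.

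| Margin | True difference | Within-subject SD 0.46 | SD of difference 0.46 | N for 80% power (within-subject SD 0.46) |
|---|---|---|---|---|
| 0.35 | 0 | 81% | 98% | 30 |
| 0.30 | 0 | 68% | 93% | 39 |
| 0.25 | 0 | 53% | 82% | 56 |
| 0.20 | 0 | 37% | 63% | 86 |
| 0.35 | 0.10 | 53% | 82% | 56 |

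The last row needs the same N as margin 0.25 because 0.35 − 0.10 = 0.25.

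**The case against.** The strongest reply is that Objectives is the outlier. The Introduction asks whether dietary restriction lowers serum potassium. The Abstract, Trial design, Sample size and Statistical methods all fit a trial of that difference, and the sample size reproduces on that basis. Rewording one sentence would then be enough. This stands as one legitimate repair, and the choice belongs to the sponsor. It does not remove the conflict in the present text.

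A second reply is that a journal article condenses a fuller protocol, and a margin may sit there or in an analysis plan. That is fair, so the missing margin is not the main charge. A margin elsewhere would still contradict the superiority label and leave the sample size justified as a test against zero.

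A reader might infer that the investigators intend to report a non-significant difference as proof of non-inferiority. The documents do not support that. Statistical methods says what p < 0.05 will be called and is silent on how a larger p-value is to be interpreted. Nor is non-significance the only route to support: significantly lower potassium on the liberalized diet would also count, and the Introduction explains why the effect of fruit and vegetable potassium is hard to predict.

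The sizes also need care. The 19% is one minus the planned power, the 2.5% holds by construction, and the first figures fall sharply if 0.46 is the SD of the difference.

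**Conclusion.** The contradiction is plain in the text and should be resolved before any data are seen. As written, the analysis cannot establish non-inferiority; it can show a difference in either direction, or fail to show one. The chance that a true rise of 0.35, the plan's own important difference, ends as non-significant is between 2% and 19%. For a true rise of 0.25 it is between 18% and 47%. These ranges assume 30 complete pairs, a two-sided 5% test and one or other reading of the SD; the contradiction depends on none of them.

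A reader might also infer that thirty participants is the wrong number. That is not shown. With a margin of 0.35 and a true difference of zero, N = 30 gives 81% power even on the less favourable SD reading. It falls short of 80% on that reading for any of the smaller margins tabulated, or for a true rise of 0.10.

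**What to change.** State one framework in Objectives, Trial design, Sample size and Statistical methods.

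**If non-inferiority is kept:**

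- Replace the superiority label in Trial design.
- Prespecify and justify a margin no larger than the 0.35 mEq/L the plan calls clinically important. Accepting the whole of a binder's starting-dose effect as a tolerable loss needs its own argument.
- Conclude non-inferiority only if the upper limit of the two-sided 95% confidence interval for liberalized minus standard serum potassium at the period endpoints (weeks 8 and 16) lies below the margin.
- Require the completers analysis, already planned, to agree. Poor adherence shrinks the diet contrast and favours non-inferiority under a confidence-limit rule too.
- State that p > 0.05 is not evidence of non-inferiority.
- Restate power for this test at the chosen margin and a plausible true difference, saying which SD 0.46 is.

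**If superiority is kept:** reword the primary hypothesis as a difference in serum potassium and make no non-inferiority claim.

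Either route is a change of wording and needs no extra data on the participants already planned. The price of the first is that the stated power may look less favourable. If the sponsor wants 80% power at a margin below 0.35 and 0.46 is the within-subject SD, the sample would have to grow as tabulated.

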### Trial design

This study is an open-label, randomized 2-period crossover definitive superiority trial. The study will be sixteen weeks in duration. Thirty male and female individuals living with CKD will be recruited, with a minimum 40% of each sex. Participants will be randomized to receive both restricted (standard care) and liberalized (experimental) K content fruit and vegetables for six weeks.

## Methods: participants, interventions and outcomes

### Study setting

This clinical trial will take place in Winnipeg, Manitoba, Canada. Recruitment of patients will happen from renal clinics at both Health Sciences Centre and Seven Oaks General Hospital. This trial has the potential to lead to beneficial changes in dietary recommendations for K intake among individuals with CKD in Canada.

### Eligibility criteria

The inclusion criteria include individuals who are over the age of 18, have an eGFR between 15 and 45 ml/min/1.73m^2^, have serum potassium levels between 4.9 and 5.5 mEq/L and a hemoglobin A1C ≤ 11%. Furthermore, participants included in this study must be registered at a multidisciplinary nephrology clinic in Winnipeg and must be able to communicate in English in order to provide written informed consent.

Individuals will be excluded from the study if:

Serum potassium > 5.5 or < 4.9 mEq/L.They have anuria, are on dialysis or have had acute kidney injury failure within six months prior to screening.Chronic obstructive pulmonary disease that requires one to be on oxygen.Have had a myocardial infarction or stroke in the past 6 months.Are currently on potassium binding therapy.Have class 3–4 heart failure symptoms or have had their liver, heart or kidneys transplanted.Unable to consume study treatments or control, such as swallowing or GI issues.People who are pregnant or lactating.Any individuals in the opinion of the investigator with any medical condition, uncontrolled systemic disease or concurrent illness that would decrease the study compliance or jeopardize the safety of the participant.

Once participants have been consented they will undergo a baseline study visit to confirm their eligibility to be enrolled into the study. During the baseline visit, anthropometric measures and blood pressure in triplicate will be collected. Participants will also be asked to complete the Kidney Disease Quality of Life Short Form (KDQOL-SF) questionnaire and the Automated Self-Administered 24-hour Canada (ASA24®) dietary assessment tool prior to being randomized to an intervention (Appendix B and Appendix C). Additionally, participants will then undergo a five repetition stand time (STS5) test that will be utilized to assess their physical function in regard to strength, mobility, balance and fall risk. Information on concomitant medications or supplements information will be obtained from the participant’s clinical records. Clinical chemistry, such as HbA1c, albumin, bicarbonate, calcium, sodium, potassium, chloride, creatinine, glucose, phosphate, as well as urea, urine albumin creatinine ratio and urine electrolytes. These will be collected and analyzed by Shared Health Manitoba which includes both blood and urine sampling. Once eligibility is verified and the participant is enrolled, they will be placed on the liberalized dK + via fruit and vegetables diet run-in for 2 weeks (intervention described below), prior to randomization.

A safety assessment will be conducted one week after baseline to ensure participants meet the eligibility criteria and that it is safe for them to continue on to the randomization stage.

## Interventions

### Intervention descriptions

Once the baseline, run-inand safety assessments have been completed, participants will be randomized into one of the two interventions:

*Liberalized dK + via fruit and vegetables (Experimental group)*.

This group will receive weekly supplementation of higher K fruit and vegetables via home delivery during the liberalized dK run in and treatment period. The weekly deliveries will contain combinations of fresh, frozen and dried fruit and vegetables, as well as juices and low-sodium soups which have been selected for their K content and shelf-life. Contents may vary throughout the intervention period based on price and availability. Participants will receive weekly deliveries of K rich fruit and vegetables that contain more than 250 mg of K per 100 g serving, such as potatoes, legumes, beets, carrots, oranges and pears. prior to the run-in week, participants will receive a 30-60-minute counseling session from the study registered dietitian (RD), where they will be instructed to incorporate the fruit and vegetables into their diet targeting a daily dK intake of 2000 mg from the delivered fruit and vegetables over 3 to 4 meals, and a daily dK intake of approximately 3500 mg. During this counseling session from the study RD standard renal diet with instructions to avoid none fruit and vegetable sources of dK will be reinforced, but not the preparation of vegetables to reduce dK content.

#### Standard dK restriction (standard care group)

Participants allocated to this group will receive weekly supplementation via home delivery of lower K fruit and vegetables, that deliver less than 200 mg of K per 100 g serving, such as cauliflower, lettuce, cabbage and blueberries. Prior to starting this intervention participants will receive a 30-60-minute counseling session from the study registered dietitian (RD), where they will be instructed to incorporate the fruit and vegetables into their diet targeting a daily dK intake of 500 mg from the delivered fruit and vegetables over 3 to 4 meals and a daily dK intake less than 2000 mg. During this counseling session from the study RD standard renal diet with instructions will be reinforced, including the preparation of vegetables to reduce dK content.

